## **5.2 Screening before enrollment**

After provided written consent, all patients (1000 patients) meeting the inclusion criteria and not meeting the exclusion criteria will receive an AMCE examination during 30-120 hours after PCI (gut purge is not allowed on the day of PCI) and a *Helicobacter Pylori* (HP) breath test, in order to identify the baseline level of gastrointestinal mucosal lesions and HP infection. Patients undergoing successful screening AMCE examination and with no ulceration or bleeding will be enrolled (at least 750 patients) and treated with open-label aspirin (100 mg/d) plus clopidogrel (75 mg/d) for 6 months. Additionally, blood routine test and fecal FOB test will be performed every 2 months after enrollment.

## **5.3 Subject randomization and initiation of investigational product**

A second AMCE examination will be performed to evaluate eligibility for randomization in all enrolled patients at 6 months after PCI. Subjects with any one of items below should not be randomized:

1. Withdrawal of informed consent;
2. Lost to follow-up at 6 months;
3. Any event in the prior 6 months which in the opinion of the investigator results in the patient not being suitable for randomization of antiplatelet agent regimen either because of a) necessity to continue dual antiplatelet therapy (e.g., major adverse cardiovascular or cerebrovascular event within the prior 6 months or need for repeat stenting), or b) inability to continue dual antiplatelet therapy (e.g., bleeding, neoplasm, need for urgent surgery, etc. within the prior 6 months);
4. Not presently taking both aspirin and clopidogrel, or any prior temporary discontinuation of aspirin or clopidogrel for  $\geq 5$  days;
5. Proton pump inhibitors or any other kind of gastric mucosal protectant agents may not be used after study enrollment unless a clear clinical indication has developed (e.g., new gastrointestinal bleeding or ulcer disease). After

randomization, gastric mucosa protectants may not be taken for more than 4 days continuously or in total for  $\geq 10$  days without a clear clinical indication.

6. Unwillingness or inability to undergo the 6-month AMCE examination or the remainder of the study procedures, including the 12-month AMCE exam.

Patients successfully completing the 6-month follow-up AMCE exam and with no ulceration or bleeding (approximately 480 patients) are then randomly assigned in a 1:1:1 ratio to receive three antiplatelet strategies below: Group A, the standard DAPT (160 patients, aspirin plus clopidogrel); Group B, aspirin monotherapy (160 patients, aspirin plus clopidogrel-placebo); and Group C, clopidogrel monotherapy (160 patients, clopidogrel plus aspirin-placebo) for an additional 6 months in a double blinded manner. A third AMCE examination will be done at 12 months after enrollment.

After randomization, patients should also undergo blood routine test and FOB test every 2 months. Moreover, the first 102 enrolled patients (34 per group) from the site of PI (General Hospital of Northern Theatre Command) will undergo platelet function testing, including adenosine diphosphate-induced platelet aggregation by light transmission aggregometry and VerifyNow aspirin and P2Y12 testing assessment.

Patients who are ineligible for randomization will not receive any more study drugs, and subsequent antiplatelet therapy will be administered at their attending physicians' discretion in accordance with the local standard of care. All enrolled patients, irrespective of eligibility for randomization, should be followed up by telephone until 12 months.

## **5.4 Procedures for handling subjects incorrectly enrolled or randomized on investigational product**

Subjects who are incorrectly enrolled will be immediately withdrawn from the study. The subject and the treating physician will be notified. If the subject has already been randomized, the study drug will be discontinued and further treatment will be per standard of care.

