### **5.9.2 Permanent discontinuation from study medication due to reasons below:**

- Patient decision. The patient is at any time free to discontinue treatment, without prejudice to further treatment.
- Investigator's decision:
  - 1) Incorrectly enrolled patient in whom the inclusion/exclusion criteria violation would put the patient at undue risk.
  - 2) Investigators judge that due to adverse events related to any kind of study drug, continuous administration of this study drug would put the patient at undue risk.

Details on the date, duration and cause of each permanent discontinuation of study drugs should be fully recorded into the appropriate section of the EDC. When any of the study drugs are permanently discontinued, further antiplatelet therapy should be given to the subject according to attending physician's discretion. Any remaining study drugs should be returned to the local research site at the next scheduled follow-up visit. Although these subjects are no longer receiving any study drug, they should also be followed up until 12 months. Patients who permanently discontinue study drugs after randomization are still required to undergo AMCE examination, and investigators are required to withdraw study drugs from patients after discontinuation. Patients who permanently discontinue study drugs before randomization only needed to be followed up by telephone at 12 months.

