## **5.10 Withdrawal from study**

Each enrolled subject shall remain in the trial until completion of the required follow-up period. However, a subject's participation in any clinical trial is voluntary and the subject has the right to withdraw at any time without penalty or loss of benefit. Conceivable reasons for discontinuation may include, but not be limited to, the following:

- Subject voluntary withdrawal
- Subject withdrawal by physician as clinically indicated
- Subject lost-to follow-up

The reason for subject discontinuation must be documented on the CRF and source documents. The principal investigators must also report all subject discontinuations to their Ethical Committee as defined by their sites' procedure. All data from

evaluations and treatments performed prior to the withdrawal should be documented on the CRFs. Source documents that pre-date the withdrawal should be submitted as required by the protocol. No data that post-dates the withdrawal will be collected.

Once a subject has withdrawn from the trial, no further follow-up contact will be performed. However, vital status may be obtained from public records. Medical therapy after stopping the study will be as prescribed by the subject's physician.

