## **6 Analysis sets**

### **6.1 Full analysis set (FAS)**

All patients who have been randomized to study treatment will be included irrespective of their protocol adherence and continued participation in the study. Patients will be analysed according to their randomized study drug assignment (not to which treatment they actually received) irrespective of whether the event occurred before or following discontinuation of study drug. Patients who withdraw consent to participate in the study (or are lost to follow-up) will be included up to the date of

their study termination except for vital status known through public records (for use in the analyses of deaths). All primary, secondary, and exploratory efficacy variables will be analyzed using the FAS. The primary endpoint of gastric or intestinal mucosal injury will be analyzed in a modified intention to treat (mITT) population, (i.e., patients with valid primary endpoint results). Unless otherwise stated, the FAS will be considered the primary analysis set for the primary and secondary variables and for the exploratory variables.

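### Protocol 5.4 withdraws incorrectly enrolled patients with no stated exception after randomisation, which conflicts with 5.9.2 and can cost the 12-month AMCE outcome

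*Supplement*

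**What the plan says.** - **Protocol v1.4, 5.4** (heading covers subjects incorrectly enrolled or randomised): "Subjects who are incorrectly enrolled will be immediately withdrawn from the study". It then adds: "If the subject has already been randomized, the study drug will be discontinued and further treatment will be per standard of care". It does not mention follow-up or the 12-month AMCE.
- **Protocol 5.10**, on withdrawal: "No data that post-dates the withdrawal will be collected", and "Once a subject has withdrawn from the trial, no further follow-up contact will be performed". Vital status from public records is the only exception. The listed reasons are open-ended and include withdrawal by the physician.
- **Protocol 5.9.2** lists, among reasons for permanently stopping study drug: "Incorrectly enrolled patient in whom the inclusion/exclusion criteria violation would put the patient at undue risk". It goes on: "Although these subjects are no longer receiving any study drug, they should also be followed up until 12 months". It also says: "Patients who permanently discontinue study drugs after randomization are still required to undergo AMCE examination".
- **SAP 6.1**, on the FAS: "All patients who have been randomized to study treatment will be included irrespective of their protocol adherence and continued participation in the study". The same section analyses the primary endpoint in an mITT set, restricted to patients with a valid primary endpoint result.
- **SAP 4.1** gives three routes to a valid result: a completed 12-month AMCE; failing that, a new lesion at the 6-month AMCE; or a new lesion found at an examination prompted by gastrointestinal bleeding.
- **SAP 8** says the primary analyses are on all randomised subjects. It plans complete-case, best-case, worst-case and, if needed, tipping-point analyses for missing outcomes.

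**The concern.** An eligibility error found after randomisation is handled in two ways. Under 5.4 read with 5.10, the patient leaves the study and no later outcome is collected. Under 5.9.2, the patient may stop drug but stays under observation and has the AMCE. A site cannot follow both.

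The protocol names intention to treat for its primary analysis. A rule that ends outcome collection in randomised patients works against that, and an AMCE that was never done cannot be recovered at analysis. The validity rules also make the loss depend on what had already been seen in the patient, so it cannot be assumed to be random.

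**Working it through.** **1. What happens to a randomised patient in each situation**

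| Situation | Section | Follow-up to 12 months | 12-month AMCE |
|---|---|---|---|
| Incorrectly enrolled, withdrawn | Protocol 5.4 with 5.10 | No (vital status only) | No |
| Incorrectly enrolled with undue risk, drug stopped | Protocol 5.9.2 | Yes | Yes |
| Blind broken in an emergency, drug stopped | Protocol 5.5.2 | Yes | Yes |

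For comparison, enrolled patients who are never randomised are followed by telephone to 12 months (protocol 5.3). Taken literally, 5.4 gives a randomised patient less follow-up than one who was never randomised.

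**2. Who then leaves the primary analysis**

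Suppose *w* randomised patients are withdrawn under 5.4 before the 12-month AMCE, and a fraction *f* of them already have a new lesion that SAP 4.1 accepts. The 6-month route is a real one: protocol 5.3 bars randomisation only for ulceration or bleeding, so a patient with erosions at 6 months can be randomised.

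- All *w* remain in the FAS.
- *f·w* remain in the mITT set, every one as an event.
- (1 − *f*)·*w* have no valid result and drop out of the mITT set.

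The withdrawn patients who are still counted therefore have an event proportion of 1, whatever their true 12-month risk. The size and direction of any effect on the treatment comparison depend on *w* and *f* in each arm, which the documents do not give.

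**3. The plan's own sample size**

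Inputs (protocol 12.3, SAP 5): 47% on DAPT, 30% on monotherapy, 1:2 allocation, two-sided alpha 0.05, 90% power, 20% loss.

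- Pooled proportion: (0.47 + 2 × 0.30)/3 = 0.3567.
- Null term: 1.960 × √(0.3567 × 0.6433 × 1.5) = 1.150.
- Alternative term: 1.2816 × √(0.47 × 0.53 + 0.30 × 0.70/2) = 1.2816 × 0.5951 = 0.763.
- DAPT arm: (1.150 + 0.763)²/0.17² gives 127 after rounding up, so 381 in total. The plan states 384.
- Power with 128 and 256: Φ[(0.17 × √128 − 1.150)/0.5951] = Φ(1.30) = 0.903. The plan states 90%.
- Randomised: 384/0.80 = 480, as stated.

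The plan's figures reproduce.

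**4. Effect of extra loss on power**

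The rate of incorrect enrolment is an assumption. Each row adds a loss *e* of the 480 to the planned 20%: evaluable N = 480 × (0.80 − *e*), with one third on DAPT. This takes every such patient as lost, so it overstates the effect on power if some have an earlier valid lesion.

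| *e* | Patients | Evaluable | Power |
|---|---|---|---|
| 0 | 0 | 384 | 0.903 |
| 1% | 4.8 | 379.2 | 0.900 |
| 2% | 9.6 | 374.4 | 0.896 |
| 5% | 24 | 360 | 0.884 |

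For 5%: Φ[(0.17 × √120 − 1.150)/0.5951] = Φ(1.197) = 0.884.

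**The case against.** **The last sentence of 5.4 may limit the action.** The heading distinguishes enrolment from randomisation, and the final sentence gives a separate action for patients already randomised: drug stops and standard care follows. On that reading 5.9.2 governs, and the AMCE is kept. This is a fair reading, but 5.4 does not say so and its withdrawal sentence carries no exception. The point therefore stands as a conflict that needs resolving, not as proof that sites would drop these patients.

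**The FAS is intact.** A reader might infer that 5.4 removes patients from the all-randomised set. It does not: SAP 6.1 keeps them whatever their continued participation. What is lost is the outcome, and usually with it the place in the mITT set.

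**Some results survive, and missing outcomes are examined.** This is correct. Losing the 12-month AMCE is not the same as losing a valid result, because SAP 4.1 accepts earlier lesions. But that same rule makes the loss outcome-dependent, and SAP 8 addresses missing outcomes only in sensitivity analyses.

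**Loss that differs by arm.** A reader might infer that errors come to light more often on DAPT, through bleeding or symptom work-ups. The documents do not show this. The trial is double-blind, baseline eligibility is fixed before allocation, and a bleeding work-up that finds a new lesion is itself a valid endpoint. Arm-dependent discovery remains possible but unsupported.

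**Conclusion.** The concern holds as a conflict between protocol 5.4 (read with 5.10) and 5.9.2. Followed as written, 5.4 ends outcome collection for a randomised patient found to have been incorrectly enrolled. That patient then leaves the mITT primary analysis unless an earlier new lesion already counts. The exclusion is avoidable and depends on outcome.

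The size is unknown, because no rate of incorrect enrolment is given. At an assumed 1% to 5% of 480 (about 5 to 24 patients), power falls from 0.903 to between 0.900 and 0.884. A reader might infer a material loss of power, but these figures do not support it. What is at stake is possible bias and adherence to the intention-to-treat principle. The documents establish neither a direction of bias nor a difference between arms.

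**What to change.** Reconcile 5.4 with 5.9.2 and 5.10 by separating leaving the study from stopping study drug. For patients found ineligible after randomisation, 5.4 should state that they:

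- remain in the study, and in the FAS in their assigned arm;
- have outcome follow-up to 12 months, including the scheduled 12-month AMCE, where consent stands and the eligibility violation is not itself a contraindication to the examination;
- are recorded as an eligibility deviation.

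The AMCE condition is needed because exclusion criteria 9 and 22 concern contraindications to AMCE and MRI, so some patients found ineligible could be unsuitable for the examination.

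Sections 5.4 and 5.9.2 also differ on when study drug stops: for every incorrectly enrolled patient already randomised, or where the violation creates undue risk. The sponsor must reconcile these; no view is offered here on which should apply.

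The cost is one protocol paragraph. The 12-month AMCE is already in the visit schedule for randomised patients. The small downside is that a few ineligible patients stay in the primary analysis set, as intention to treat requires.

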## **5.5 Blinding and procedures for unblinding the study**

This study has a double-blind design with aspirin, clopidogrel and their corresponding placebos. Neither the subjects, study site research personnel, or treating physicians involved in the treatment or clinical evaluation of the subjects will be aware of treatments received. There will be an independent data safety monitoring board (DSMB) to monitor the data on a periodic basis.

### **5.5.1 Methods for ensuring blinding**

This study has a double-blind design with aspirin, clopidogrel, and matching placebos. Shenyang Yu Kang Pharmaceutical Technology Co., Ltd, a statistical organization independent of the study, used SAS software to generate random codes for the corresponding groups (primary blind codes), and the study drug regimen corresponding to the group (secondary blind codes), and import the two levels of blind codes (including primary and secondary blind codes) via the Taimei Medical Randomization and Drug Management System (eBalance). Randomization is stratified according to site and will be performed in fixed block. The active tablets and the respective placebo tablets will be identical in size, color, smell, and taste. The patients, site personnel, sponsor personnel, persons performing the assessments, and data analysts will remain blinded to the identity of the treatment from the time of randomization until completing the statistical analysis. There will be an independent data safety monitoring board (DSMB) to monitor the data on a periodic basis.

### **5.5.2 Methods for breaking the blinding in the study**

In the event of a medical emergency, in which knowledge of the investigational drug is critical to the subject's medical management, the blind for that subject may be broken by the treating physician. Before breaking the blinding, the consent of the research leader of the participating research site should be obtained and the relevant researchers and monitors should be informed. At the same time, the events leading to break the blinding and the blind code information should be recorded in detail. After breaking the blinding, the subject will not receive any study drug, and the treated physician can take corresponding bail-out measures according to local standard of care. The study drugs cannot be resumed even if the condition of subject is stable, while researchers still need to conduct clinical follow-up for 12 months for the subject with broken blinding, and AMCE examination is still required. Researchers should withdraw the study drugs from the patients whose blinding was broken.

### **5.5.3 Methods for unblinding in the study**

Unblinding will be conducted after the whole study procedure. Because of the randomized, double-blinded, placebo-controlled study design, a two-level unblinding (first and second unblinding) is prespecified. The whole procedure of unblinding is organized by Data and Safety Monitoring Boards (DSMB), and collectively witnessed by representatives of research sites, contract research organization (CRO) and statistical organization. The unblinding should not be

performed until completing the statistical analysis.

The first unblinding: Only the definite group (such as group A, group B, and group C) of each subject is unblinded, but the study drug corresponding to each group is not clear yet. At this time, the information of study drug will be filed by statisticians for statistical analysis.

Second unblinding: After the statistical analysis is finished, a statistical report will be generated. The primary investigator will perform the second unblinding when publishing statistical results, and simultaneously announce the study drug of each group, then combine the blind codes to generate the final statistical results.

## 5.6 Treatments

### 5.6.1 Identity of investigational product

In this protocol, the investigational product is aspirin 100 mg tablets and matching aspirin-placebo tablets, and clopidogrel 75mg tablets and matching clopidogrel-placebo tablets.

**Table 1 Identity of Investigational Product**

| Study drug              | The form and dosage of drug | Manufacturer                                      |
|-------------------------|-----------------------------|---------------------------------------------------|
| Bayaspirin
(aspirin) | 100mg tablet                | Bayer                                             |
| Aspirin-placebo         | tablet                      | Guangzhou Boji Medical Biotechnological co., Ltd. |
| Plavix
(clopidogrel) | 75mg tablet                 | Sanofi-Aventis                                    |
| Clopidogrel-placebo     | tablet                      | Guangzhou Boji Medical Biotechnological co., Ltd. |

### 5.6.2 Doses and treatment regimens

After enrollment, patients will routinely administer study drugs (including open-label aspirin at a dose of 100mg swallowed with 100ml warm water 30 minutes daily before breakfast, plus open-label clopidogrel at a dose of 75mg daily) until the face-to-face study visit at 6 months. At the face-to-face study visit, randomized participants will be allocated study drugs (including: Group A, blinded-label aspirin at a dose of 100mg daily, plus blinded-label clopidogrel at dose of 75mg daily;

Group B, blinded-label aspirin at a dose of 100mg daily, blinded-label clopidogrel-placebo at dose of 75mg daily; Group C, blinded-label aspirin-placebo at a dose of 100mg daily, plus blinded-label clopidogrel at dose of 75mg daily) and should be used regularly until the end of study.

### **5.6.3 Rationale and procedures of AMCE**

ANKON® magnetically controlled capsule endoscopy system (AMCE), which is provided by ANKON Medical Technologies (Shanghai, China) and ANKON Photoelectric Technology Co., Ltd (Wuhan, China, ANKON Enterprise), is composed of a magnetic navigation control system, a portable data recorder and a capsule position detector. The capsule endoscope (known as an endoscopic robot) has a length of 27 mm and a diameter of 11 mm and contains a permanent magnet. It provides a 140° viewing angle, a 30 mm depth of field and operates for at least 10 hours after ingestion. The activated capsule is swallowed into the digestive tract and continually records the condition of digestive tract mucosa. The dimensions of any visualized lesions are measured by the ANKON ESNavi software. After reaching the gastric cavity, the endoscopic capsule is navigated by the external magnetic control system to visualize all aspects of the stomach (the cardia, fundus, angulus, antrum, and pylorus). The controller allows movements of 2 mm and changes in viewing angle of 3°. AMCE is the first actively and accurately capsule gastroscope robot that could actively and precisely provide the whole gastric examination. Multicenter, large-scale randomized studies have demonstrated that the accuracy and specificity of AMCE system was high consistent with standard gastroscopy.

Preparation before AMCE examination: Patients fasted on food, colored liquid or syrup from 8 pm the day before AMCE examination. Gut purge shall be done 6-8 hours before examination. On the following morning the subject is administered 10 ml of simethicone (Menarini Group, Florence, Italy) as a defoaming agent to clean the stomach cavity 40 minutes before the examination, and drinks water (500-1000 ml) until feeling stomach fullness. During examination, if the gastric cavity is not filled with sufficient liquid to enable navigation of the capsule, the subject will drink additional water.

After the whole stomach is examined, subjects continue to wear the portable recorder for visualization of the duodenum and small intestine. After examination of the whole stomach, subjects could leave the hospital but should continue to wear the portable recorder for examination of the small intestine. that Subjects should return to the hospital as soon as possible once the instrument suggests that the whole examination is finished, and are subsequently followed up for up to 2 weeks to determine if the capsule is ultimately excreted or adverse events occur. Subjects should record the time when the capsule is discharged with defecation. The capsule can be abandoned after elimination without recycling. Magnetic resonance imaging is prohibited before the confirmation of capsule excretion. If the capsule is not found to be excreted within 2 weeks after examination, the subject returns to the hospital

for detection of the capsule by a position detector or abdominal x-ray to confirm whether the capsule is still in the body. If it is, endoscopy may be performed to remove the capsule.

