### **6.2.3 Face-to face follow-up procedure at 12 months (for randomized subjects)**

- Assess for adverse events may include, but not be limited to MI, stroke, revascularization, bleeding and ST
- Conduct the third AMCE examination to observe gastrointestinal mucosal lesions
- Review concomitant medications with subject
- Recycle and count all of remaining study drugs

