## **7.3 Recording of adverse events or serious adverse event**

### **7.3.1 Time period for collection of adverse events**

All AEs related to cardiovascular, cerebrovascular and gastrointestinal aspects and all SAEs should be collected from the time the subject signs the informed consent through study exit.

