### **12.1.2 Safety analysis set**

Safety analyses of study medications will be performed on the FAS population. The safety endpoint is MACCE defined as a composite of cardiac death, target lesion MI, ischemic stroke, clinical-driven TLR or stroke within 12 months after enrollment.

Safety analyses of AMCE examination will be performed in patients undergoing AMCE examination (including GI cleansing). The safety endpoints are digestive symptoms (abdominal distension, nausea, or vomiting, etc.) and retention of capsule endoscopy within 30 days.

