### **4.3 Safety variables**

Adverse events (AEs) of interest (i.e., abdominal distension, nausea, or vomiting after AMCE examination within 1 month) will be collected throughout the study period.

All serious adverse events (SAEs) will be recorded from the time of informed consent throughout the study.

Section 7 in the Protocol gives more detailed information on adverse event data collection.

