## **6.3 Safety analysis set**

There are 2 safety sets (SSs) in OPT-PEACE trial. Safety and tolerability will be assessed from serious adverse events (SAEs) and adverse events (AEs). The assessment will include MACCE defined as a composite of cardiac death, target lesion MI, ischemic stroke, clinical-driven TLR or stroke in SS (investigational drug) and the incidence of AEs related to AMCE examination and capsule retention in SS (AMCE examination). All events will be independently adjudicated.

The first safety analysis set includes patients who received at least 1 dose of study drugs (aspirin, clopidogrel, and/or matching placebos) and who have data observed at any time after first randomized dose until the end of the study. The safety endpoint is MACCE defined as a composite of cardiac death, target lesion MI, ischemic stroke, clinical-driven TLR or stroke within 12 months after enrollment. Throughout the safety results sections, erroneously treated patients (patients randomized to one of the treatment groups but actually given the other treatment) will be accounted for in the actual treatment group. Patients with erroneous treatment would be analyzed according to that treatment only if they only received the erroneous treatment and none of the correct treatment.

The secondary safety analysis set includes patients who received AMCE exam at least once and observed up to 30 days for safety surveillance. The safety analysis set will be considered the primary analysis set for AMCE as a method for detecting gastrointestinal mucosal injury and bleeding. The safety endpoint is 1) adverse events, defined as symptoms or signs such as abdominal distension, nausea, or vomiting; 2) capsule retention (i.e., a capsule endoscope remaining in the digestive tract for a minimum of 2 weeks or a capsule endoscope that requires directed intervention or therapy to aid its passage).

All safety variables will be analyzed using the safety analysis set.

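### The AMCE symptom endpoint is stated over 30 days, but AMCE-specific follow-up stops at 2 weeks, leaving days 15–30 without planned observation after the third exam and probably for screened patients who are not enrolled

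*Supplement*

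**What the plan says.** Three places set a window of about a month for AMCE safety.

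- Protocol v1.4, 12.1.2 gives the endpoints as digestive symptoms and "retention of capsule endoscopy within 30 days".
- SAP 4.3 names the events of interest as "abdominal distension, nausea, or vomiting after AMCE examination within 1 month".
- SAP 6.3 defines the AMCE safety set as "patients who received AMCE exam at least once and observed up to 30 days for safety surveillance".

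The procedure section is shorter. Under protocol 5.6.3, subjects "are subsequently followed up for up to 2 weeks to determine if the capsule is ultimately excreted or adverse events occur". It adds: "If the capsule is not found to be excreted within 2 weeks after examination, the subject returns to the hospital" so that the capsule can be located. SAP 6.3 counts a capsule as retained once it has stayed at least 2 weeks or has needed intervention.

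The general safety net is in protocol 7.3.1: gastrointestinal adverse events and all serious adverse events are "collected from the time the subject signs the informed consent through study exit". Protocol 5.2 and 5.3 add blood and stool tests every two months and telephone follow-up of enrolled patients to 12 months. The task list for the final visit (protocol 6.2.3) includes "Conduct the third AMCE examination to observe gastrointestinal mucosal lesions", and Table 2 schedules nothing after that visit.

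**The concern.** A rate reported as a 30-day rate should rest on 30 days of observation for everyone in its denominator. Here the denominator is everyone with at least one AMCE, while the exam-specific follow-up stops at day 14. For exams where nothing else continues after day 14, a patient with late bloating, nausea or vomiting would be counted as symptom-free because no one was due to ask. The reported rate could then look better than it is. AMCE safety is part of a stated secondary objective, so the window matters for how that result can be described.

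**Working it through.** The documents give no power or precision figure for AMCE safety, so there is no stated number to reproduce. The check compares windows and counts exams.

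**Windows**
- Endpoint window: 30 days (protocol 12.1.2, SAP 6.3) or 1 month (SAP 4.3).
- AMCE-specific follow-up: up to 14 days (protocol 5.6.3).
- Difference: 30 − 14 = 16 days, and 16/30 = 53% of the window.

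**What else covers days 15–30**
- *First exam, enrolled patients.* About 12 months of study follow-up remain, so day 30 lies inside adverse-event collection. The next scheduled test is at about two months, so mild symptoms rest on spontaneous report or recall.
- *Second exam.* About 6 months remain, and the same reasoning applies.
- *Third exam.* It takes place at the last scheduled visit. Protocol 6.2.1 and 6.2.2 tell staff to ask subjects to report adverse events; the 12-month list in 6.2.3 does not. Study exit is not defined in relation to the last AMCE.
- *Screened but not enrolled.* Telephone follow-up in protocol 5.3 is for enrolled patients, and protocol 5.2 enrols only those with a successful screening exam without ulceration or bleeding. Protocol 12.1, however, defines the Enrolled Population as everyone who signed consent, so coverage is unclear.

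**Planned exams**
- First exams: 1000 (protocol 12.3).
- Screened, not enrolled: 1000 − 750 = 250.
- Second exams: between 750 (all enrolled) and 0.83 × 750 ≈ 622 (less the 17% noncompliant with the 6-month exam).
- Third exams: between 480 (all randomized) and 384 (the evaluable number).

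| Second | Third | Total | Third exam share | Not-enrolled share | Both |
|---|---|---|---|---|---|
| 750 | 480 | 2230 | 21.5% | 11.2% | 32.7% |
| 750 | 384 | 2134 | 18.0% | 11.7% | 29.7% |
| 622 | 480 | 2102 | 22.8% | 11.9% | 34.7% |
| 622 | 384 | 2006 | 19.1% | 12.5% | 31.6% |

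Each share is the count divided by the row total; for example, (480 + 250)/2102 = 34.7%. The remaining 65–70% of exams fall inside continuing study follow-up.

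**Retention**
A capsule still in place at day 14 already meets the SAP definition, and one that needed intervention earlier meets it sooner. Protocol 5.6.3 sends a subject without known excretion back to hospital at that point. The check falls when the definition can first be met on duration, after all three exams.

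**The case against.** A reader might infer that the 30-day endpoint goes unobserved after every exam. The documents do not support that. Enrolled patients after the first two exams remain under gastrointestinal adverse-event collection for months, with two-monthly tests and instructions to report events. What they lack is a contact within days 15–30.

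A reader might also infer that retained capsules would be missed or under-counted, with consequences for the MRI prohibition. That is not supported either: protocol 5.6.3 requires a return visit when excretion is not found within 2 weeks, and any retention that is a serious event is followed until it resolves or stabilises (protocol 7.3.2). The check does depend on the subject recording excretion, but that is a smaller matter.

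Other points on this side have weight. The 2-week follow-up is not limited to the first two exams, so it runs past the 12-month visit. Study exit is not stated to be the day of that visit. The words *up to* in SAP 6.3 can be read as a maximum. In protocol 12.1.2 the 30 days may attach to retention alone. Follow-up of screen failures is ambiguous, not plainly absent. AMCE safety is summarised for the set as a whole, with no comparison between arms.

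These points narrow the concern but do not remove it. SAP 4.3 attaches one month to symptoms explicitly, and no procedure delivers days 15–30 after the last exam.

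**Conclusion.** The point holds for digestive symptoms. The stated window is 30 days or 1 month and the AMCE-specific follow-up is 14. Days 15–30 have no planned observation after the third exam (384–480 exams, about 18–23% of the total), and probably none for about 250 screened patients who are not enrolled (about 11–12%). Together that is about 30–35% of planned exams. For the rest, those days are covered only by general adverse-event collection and later recall.

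The shares assume the planned numbers, the ranges above for second and third exams, no unscheduled exams, and the narrower meaning of enrolment in protocol 5.2. If the wider meaning in protocol 12.1 governs follow-up, only the third-exam share remains. The documents give no rate of late symptoms, so the number of events missed cannot be estimated; the 53% counts days, not events.

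Retention by the SAP definition and the primary efficacy analysis are unaffected. The inconsistency should be resolved before the AMCE safety result is reported as a 30-day rate.

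**What to change.** Use one window throughout.

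- **Preferred: state what is observed.** In protocol 12.1.2, SAP 4.3 and SAP 6.3, give the AMCE symptom and retention window as 2 weeks, matching protocol 5.6.3, with retention status taken from the check at the end of that period. The cost is wording only, with a more modest claim.
- **Alternative: keep 30 days and observe them.** Add a short day-30 telephone contact after each AMCE, at least after the third exam and for screen failures, to protocol 5.6.3, both schedule tables and SAP 3.6. Define study exit in protocol 7.3.1 as no earlier than day 30 after the last AMCE. The cost is one short call per exam and a slightly later database close.

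Under either option, say whether patients who fail the screening exam count as enrolled for follow-up, since protocol 5.2 and 12.1 use the word differently.
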